## Abstract

Mental fatigue, induced by prolonged cognitive demands, impairs attention, decision-making, and motor coordination, potentially compromising performance in cognitively demanding sports such as football. This study presents a randomised controlled experimental design pre-test/post-test protocol designed to investigate the effects of mental fatigue on neurophysiological, visual, technical, and motor performance in football players. Thirty-four athletes (17 men, 17 women; aged ≥18 years; ≥1-year competitive experience) will be randomly assigned to either a cognitive fatigue induction group (30 min Stroop Task) or a low cognitive load control group. Data collection will include EEG (theta and alpha bands), eye tracking (fixation, saccades, pupil dynamics), sport-specific tasks (Loughborough Soccer Passing Test, Y-Shaped Agility Reaction Test), and subjective fatigue ratings (Fatigue Assessment Scale; Visual Analogue Scale). Statistical analyses will encompass intra- and inter-group comparisons, correlation and regression models. By integrating subjective, physiological, and performance indicators in a sport-specific, ecologically valid design, this protocol aims to deepen understanding of how mental fatigue affects performance and to inform individualized monitoring and intervention strategies in high-performance contexts. As a protocol paper, no data are yet available. However, based on previous literature, mental fatigue is expected to be associated with changes in EEG oscillatory activity, less efficient gaze behaviour, and impaired football-specific performance compared to the control condition.

## Introduction

1

Mental fatigue is defined as a psychobiological state resulting from prolonged and demanding cognitive activity, leading to a subjective feeling of tiredness, increased perception of effort, reduced motivation, and impaired cognitive and motor performance (1, 2). These changes may lead to declining in the performance of sports tasks requiring cognitive resources, such as rapid decision-making, precise motor execution, and perceptual-motor adaptation, especially under pressurized conditions. Within the cognitive sciences the negative impact of mental fatigue on attention and executive control processes are already established (3). In sporting contexts, similar evidence is accumulating (4, 5). Dynamic sports performance—demanding quick responses, motor precision and rapid decision-making under pressure—may be particularly vulnerable to the effects of mental fatigue. Several studies show that mental fatigue compromises technical performance, reduces reaction speed and impairs motor accuracy in competition (1, 4, 6, 7).

Performance declines, caused by mental fatigue, have been investigated through behavioral, neurophysiological and perceptual measures, with robust evidence, demonstrating impairments in the cognitive and motor sport tasks (1, 3, 7). High cognitively demanding tasks, such as Stroop Task (ST), are frequently applied in experimental protocols for induction of mental fatigue, due to their sustained engagement of attention and inhibition regulation systems. Such tasks also exert detrimental effects on subsequent performance; affecting both technical execution and physical preparedness (4, 8). Moreover, some studies confirm mental fatigue has deleterious effects on reaction time, motor accuracy, and decision-making, in particular when there is a need for rapid adjustments and fast responses under stress (1).

Collectively, existing literature highlights that high energy costs and reduced motivation—driven by prolonged cognitive efforts—are at the root of mental fatigue's negative impact (9–11). These effects include a reduction in reaction time, increasing technical errors, diminishing motor accuracy, and disruption of perceptual-attentional strategies: All important functions for cognitively complex tasks, such as football match-play (2, 12). Recent findings also highlight mental fatigue impairs neuromuscular coordination and cortical excitability during demanding physical efforts, which subsequently influences technical execution and reaction time in sport-specific scenarios (13–15).

From a neurophysiological perspective, mental fatigue often manifests as an increase in theta and alpha power frequency bands, measured by Electroencephalogram (EEG), especially in the frontal region. These changes are associated with reduced vigilance, reduced attentional effort and less efficient executive control (16–18). Some experiments, for example Wascher et al. (19), show that frontal theta activity is highly correlated with specific components of mental fatigue, such as the depletion of attentional resources and sustained cognitive overload. These differences indicate a lower level of vigilance and a decreased information processing efficiency, which may be related to lowered attentional effort and less efficient executive control (20–23). Simultaneously, mental fatigue also compromises visual attention, a critical function underpinning perceptual-motor performance in sports tasks. Eye tracking system (ETS) enable analysis of gaze patterns (e.g., saccades, blink rate, pupil dilation, fixations), which have been validated as objective indicators sensitive to cognitive effort and fatigue status (24, 25). Recent studies show that mental fatigue compromises visual exploration efficiency and delays oculomotor response, with subsequent negative impacts on technical performance and decision-making (26, 27).

In addition, subjective measures have been widely used to capture individual perceptions of mental fatigue, offering a phenomenological perspective that complements physiological and behavioral approaches. Visual Analogue Scales (VAS), for example, are used to quantify momentary variations in fatigue status with high sensitivity and easy application (28, 29). Also, Fatigue Assessment Scale (FAS) demonstrate psychometric robustness in assessing physical and mental dimensions of fatigue and have been validated in different populations and contexts (30–33).

For behavioral assessment of sport performance, specific tools validated in the context of football also stand out. The Loughborough Soccer Passing Test (LSPT) is a standardized task that assesses technical passing accuracy under time pressure, by integrating elements of motor control, decision-making and rapid execution. This assessment has demonstrated validity and reliability in discriminating skill levels in football players and is widely used to monitor technical performance under demanding conditions (34, 35). In turn, Y-Shaped Agility Reaction Tests (Y-SART) enable quantification of agility and reaction speed in response to visual stimuli, and are particularly sensitive to the influence of fatigue on decision-making and rapid changes of direction (36). These performance tests provide objective and ecologically valid measures that could capture the impact of mental fatigue on complex motor tasks in football.

Despite growing interest in the topic, the existing literature exhibits sizeable methodological gaps. Few studies have adopted multimodal approaches that simultaneously integrate electrophysiological (e.g., EEG) and/or oculometry measures, such as those captured by ETS, subjective perceptions of fatigue (e.g., VAS) and motor performance (e.g., LSPT) in a single cohesive experimental structure. Although some studies explore the effects of cognitive load on oculometry parameters [e.g., (25, 37)], few studies simultaneously integrate neurophysiological, visual, subjective and motor measures, hindering a holistic understanding of the impact of mental fatigue in sport context. This fragmentation hinders a comprehensive understanding of the effects of mental fatigue in dynamic sporting contexts that require quick decisions and precise movements.

The absence of integrated protocols limits not only the ecological validity of results, but also their applicability to training and performance contexts. Recently, the importance of more comprehensive and ecologically valid experimental designs—simultaneously integrating assessments of athletes' physical, technical, and cognitive performance –, has been advocated in the literature (7, 27); primarily because mental fatigue diminishes not only physical and technical skills, but also interferes with the attentional resources necessary for efficient execution of football-specific tasks (2, 6, 12).

This study proposes a methodology and an experimental protocol to assess mental fatigue and its effects on physical performance in football. Subjective and objective instruments will be used to assess mental fatigue, namely: FAS, to measure the general level of physical and mental fatigue; VAS, applied at different times to capture moment variations in fatigue perception; ETS, to analyze saccades, blink rate, pupil dilation, and fixation pattern as markers of cognitive overload; and EEG, recording the brains electrical activity, with a focus on frontal theta and alpha bands associated with attention and executive control. Physical performance will also be assessed via two motor performance tests: LSPT, which assesses technical accuracy and decision-making under time pressure; and Y-SART, measuring the agility and reaction time to visual stimuli (38).

There is a clear need for an ecologically-valid, football-specific experimental protocols integrating neurophysiological, visual, subjective and sport-specific motor measures within a single, coherent design. The present protocol describes a randomised controlled pre-post protocol design to examine how acute mental fatigue affects cortical activity, gaze behaviour and technical-motor performance in football players.

This methodology combines EEG, head-mounted eye tracking during the LSPT, validated agility assessment with the Y-SART, and subjective fatigue ratings to provide a multimodal characterisation of mental-fatigue responses. Our hypothesis is that, compared to a low-load control condition, a 30 min ST will induce higher subjective fatigue, altered frontal-parietal EEG activity, less efficient visual exploration, and decrements in football-specific performance. If confirmed, these findings will support the use of this protocol as a replicable framework for research and applied monitoring in high-performance football environments.

## Materials and methods

2

### Study design

2.1

This study employed a randomised controlled experimental design, double-group pretest-posttest design, to evaluate the effects of mental fatigue on football players performance (39, 40). Due to its experimental design, the investigation will be carried out in a controlled laboratory setting where cognitive and motor tasks will be standardized and applied. The sequence of procedures and data collection moments is detailed in Figure 1, which outlines the six phases of the methodology and experimental protocol, including both pre and post intervention assessments. Although conducted in a controlled laboratory environment, this design prioritizes internal validity to isolate acute fatigue-related effects while incorporating football-specific performance tasks to preserve ecological relevance.

**Figure 1 F1:**
[figure not shown]
Study design.

Ethical approval was granted by the Ethics Committee of Polytechnic University of Coimbra (reference D96/2024), ensuring that the research complies with the ethical standards, with priority given to the well-being and rights of the participants. All procedures are in accordance with the ethical principles established in the Declaration of Helsinki, as well as with the requirements defined by the General Data Protection Regulation of the European Union (GDPR-EU2016/679).

In addition to institutional approval, the study protocol will also be registered in a public clinical trial database, promoting transparency and accountability in the research process. This registration will allow public access to the methodological details of the investigation. By securing both ethical approval and trial registration, the study commits to the principles of ethical conduct in research, ensuring that participant safety and informed consent are respected throughout the process.

### Sample

2.2

Sample size was calculated using G*Power 3.1.9.7 software (41), considering a repeated measures ANOVA design with two groups (experimental *vs.* control) factors, and two measurement times (pre *vs.* post). The estimated minimum sample size at alpha 0.05 and statistical power of 80%, for moderate effect size (f = 0.25), was approximately 34 subjects (17 per group). At baseline, participants will be pre-screened using an online questionnaire to determine eligibility.

The inclusion criteria were: (i) minimum age of 18; (ii) at least one year of competitive football experience; (iii) no eye problems that impair vision; (iv) no history of neurological injuries; (v) abstinence of caffeine, alcohol and intense physical activities in the previous 24 h before each experimental session; (vi) having slept for at least 7 h the night before. On the other hand, the exclusion criteria were: history of neurological injury; uncorrected vision problems; diagnosis of psychological disorders; use of psychoactive substances in the last 24 h before the experimental sessions; any form of nystagmus for electrophysiological contraindications for electrophysiological recording. The operationalization and description criteria are summarized in Table 1.

**Table 1 T1:** Sample operationalization and description criteria.

Topic	Description	Operationalization
Age	Minimum age of 18 years	Participants aged 18 years or older. There is no maximum age limit stipulated in the protocol.
Gender	Gender balance	Sample of 24 men and 24 women, in equal number for experimental and control groups.
Competitive experience	Minimum of 1 year of competitive experience	Football players with a minimum of 1 year of regular practice in competitive condition
Health condition	No conditions preventing the practice of sport	Individuals with a history of neurological injuries, uncorrected visual problems, diagnosed psychological disorders, use of psychoactive substances in the last 24 h, or any clinical limitation to physical exertion will be excluded. Pregnant women will also be excluded.
Legal and ethical criteria	Compliance with current regulations	The study complies with the GDPR and the provisions of Decree-Law No. 5/2007, ensuring that all participants meet the legal and ethical conditions for physical exercise.

During the previous phase, participants will receive specific instructions by e-mail one week before the experimental session, specifying preparation procedures to ensure standardized test conditions.

Upon arrival at the controlled laboratory setting (Phase 1), participants will first be reminded of the study procedures and objectives. After confirming their understanding, each participant will sign an informed consent form, in accordance with the General Data Protection Regulation (GDPR) and Portuguese legislation (Decree-Law No. 5/2007), ensuring ethical compliance and fitness for sports-related assessments. Adherence to pre-test instructions will then be verified, followed by the administration of a structured questionnaire to collect sociodemographic and sports-related information (age, gender, position on the field, training experience, weekly training load, sleep habits, caffeine intake, and history of injury). This data will be used to contextualize participants and control potential confounding variables. These variables may be considered as exploratory covariates in secondary statistical analyses to examine potential moderating effects of competitive experience and contextual factors on fatigue-related outcomes. However, the study is primarily powered to detect main fatigue-related effects rather than complex interaction models.

Following baseline assessment, all participants will be randomly assigned to either the experimental group or the control group (Phase 4). The experimental group will perform a cognitively demanding task, the ST, for 30 min, designed to induce mental fatigue through sustained attention and inhibitory control demands. Although the ST does not reproduce the full cognitive complexity of real football match situations, it is widely used in experimental research to induce a controlled state of mental fatigue under standardized conditions (4, 8). In the present protocol, it is not intended to simulate football-specific decision-making demands, but rather to induce mental fatigue prior to sport-specific performance assessment. This separation between fatigue induction and performance testing allows clearer interpretation of the neurophysiological and behavioral consequences of mental fatigue. In contrast, the control group will engage in a low-demand relaxation condition, consisting of reading neutral magazines for the same duration (30 min), thereby maintaining minimal cognitive load while controlling for time-on-task effects.

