### Statistical analysis

2.6

All statistical analyses will be performed using IBM SPSS Statistics version 29.0 (IBM Corporation, Armonk, NY, USA), with a significance level set at 5% (*p* < 0.05). Descriptive statistics (mean, standard deviation, 95% confidence intervals, and range) will be calculated for all outcome variables, including EEG spectral powers, oculomotor parameters, motor performance scores, and subjective fatigue ratings. These data will be stratified by group (experimental and control) and time (pre- and post-intervention) and presented visually using box plots and line graphs to facilitate interpretation (88, 89).

To assess the effect of mental fatigue, paired t-tests will compare pre- and post-intervention results within each group, while independent t-tests will compare the experimental and control groups at each time point (88, 90). For EEG outcomes, repeated-measures ANOVA models will include Time (pre vs. post mental fatigue) and Recording Condition (eyes open, eyes closed, motor imagery) as within-subject factors, and Group (experimental vs. control) as a between-subject factor (88, 90). Assumptions of normality and sphericity will be evaluated prior to analysis, following established recommendations for repeated measures designs (88, 91). When sphericity is violated, the Greenhouse-Geisser correction will be applied. Effect sizes will be reported using eta squared (*η*^2^), interpreted according to Marôco (90) as small (<0.04), moderate (0.04–0.25), or large (≥0.25). Statistical power (π) will also be reported when applicable (92, 93).

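### The 80% power with 34 players belongs to the within-subject tests at an unstated pre-post correlation of 0.5, not to the independent t-tests planned for the non-EEG group comparisons

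*Protocol article*

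**What the plan says.** Section 2.2 (Sample) describes a G*Power calculation "considering a repeated measures ANOVA design with two groups (experimental *vs.* control) factors, and two measurement times (pre *vs.* post"). It gives alpha 0.05 and reports that the minimum for "statistical power of 80%, for moderate effect size (f = 0.25), was approximately 34 subjects (17 per group"). It does not say whether the effect tested is Time, Group or Group x Time, and it gives no correlation between the two measurements.

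Section 2.6 (Statistical analysis) plans paired t-tests within each arm and states that "independent t-tests will compare the experimental and control groups at each time point". It introduces a repeated-measures ANOVA with Group, Time and Recording Condition for the EEG outcomes. The Discussion adds a repeated-measures ANOVA for time and group interaction without saying which outcomes it covers.

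Table 1 gives 24 men and 24 women, whereas the Abstract and section 2.2 give 34 in total.

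**The concern.** The hypothesis in the Introduction is comparative: the Stroop arm should worsen more than the low-load control arm. A reader of section 2.2 will conclude that the trial has 80% power to show a moderate effect of that kind. Two things stand in the way. First, the power of a repeated-measures calculation depends on which effect is tested and on the pre-post correlation, and neither is reported. Second, the test that section 2.6 gives for comparing the arms on the passing test, the agility test, eye tracking and the fatigue VAS is an independent t-test at each time point, which is not the test behind the calculation.

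The interpretation of a null result is at stake. If the group comparison of passing scores is not significant, the stated power invites the conclusion that a moderate effect has been made unlikely. For a 0.5 SD difference, the independent t-test would miss it about seven times in ten.

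**Working it through.** **Inputs from the article.** f = 0.25, alpha = 0.05, N = 34 in two equal arms, m = 2 times, target power 80% (section 2.2).

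**Assumption.** The pre-post correlation rho is not in the document. A value of 0.5 is used first and then varied. Tests are two-sided, with noncentral F or t distributions.

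**1. Reproducing the 34.** For Time or Group x Time, lambda = f² x N x m / (1 - rho), with 1 and N - 2 degrees of freedom.
- N = 34, rho = 0.5: lambda = 0.0625 x 34 x 2 / 0.5 = 8.5, df 1 and 32, power 80.7%.
- N = 32: lambda = 8.0, power 78.1%. So 34 is the smallest even total that reaches 80%.

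For the between-group main effect, lambda = f² x N x m / (1 + (m - 1) x rho) = 4.25 / 1.5 = 2.83. Power at N = 34 is 37.2%, and 80% needs 98. The stated figure is therefore not a calculation for the Group effect.

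**2. Dependence on rho (Time or Group x Time, f = 0.25).**

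| rho | Power at N = 34 | N for 80% |
|---|---|---|
| 0.3 | 67% | 46 |
| 0.4 | 73% | 40 |
| 0.5 | 81% | 34 |
| 0.6 | 89% | 28 |
| 0.7 | 95% | 22 |

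**3. What f = 0.25 means for each effect.**
- Time: pre and post means lie 0.25 SD either side of the overall mean, so the change pooled over both arms is 2 x 0.25 = 0.5 SD.
- Group x Time: each of the four cells deviates by 0.25 SD, so the difference in change between arms is 4 x 0.25 = 1.0 SD, whatever rho is.

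Check: the SD of change is SD x sqrt(2(1 - rho)), which equals the outcome SD at rho = 0.5. A two-sample t-test on change with d = 1.0 and 17 per arm has noncentrality sqrt(17/2) = 2.915. Its square is 8.5, and the power is 80.7%, so this is the same test.

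**4. Group x Time for a 0.5 SD difference in change, 17 per arm.** d = 0.5 / sqrt(2(1 - rho)).

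| rho | Power |
|---|---|
| 0.3 | 22% |
| 0.5 | 29% |
| 0.7 | 45% |
| 0.8 | 61% |

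**5. The planned independent t-test at one time point.** For two groups, f = 0.25 corresponds to d = 0.5.
- 17 per arm: noncentrality 0.5 x sqrt(17/2) = 1.458, df 32, power 29.3%.
- 80% power at d = 0.5 needs 64 per arm.
- With 17 per arm, the difference detectable with 80% power is 0.99 SD.

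**6. If Table 1 is right (48 in total, 24 per arm).** Power at d = 0.5 is 39.6%, and the detectable difference is 0.83 SD.

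**The case against.** The case for the plan has several parts, and most of them limit the point.

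- **The 34 is not a miscalculation.** It follows from the stated inputs at rho = 0.5. A reader might infer an arithmetic error, but there is none. An article may also leave the effect and rho to a fuller document. That excuses the omission. It does not excuse the mismatch with the t-tests, because the article states both sides of it.
- **The 80% is not confined to Group x Time.** It also holds for the Time effect pooled over arms. That is correct, but a pooled change cannot separate fatigue from control.
- **The label moderate is not contradicted.** A reader might want it removed because 1.0 SD is large on the usual two-group scale. Section 2.6 grades eta squared "as small (<0.04), moderate (0.04–0.25), or large (≥0.25"). For f = 0.25, eta squared is 0.0625 / 1.0625 = 0.059. The partial value at lambda = 8.5 is 8.5 / (8.5 + 34) = 0.20. Both lie in the article's own moderate band.
- **The remark on interactions is not a misstatement of the calculation.** Section 2.2 says "the study is primarily powered to detect main fatigue-related effects rather than complex interaction models". Read with what precedes it, and with section 2.5.5, it concerns moderation by participant characteristics, not Group x Time.
- **Some planned tests do match.** The EEG model in section 2.6 and the ANOVA in the Discussion contain the effect that was powered. The mismatch is limited to the independent t-tests. The 29% cannot be applied to the EEG comparisons without assuming rho = 0.5.

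What remains is the unnamed effect and correlation, the unstated 1.0 SD, and between-group tests for most outcomes to which the quoted power does not apply.

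**Conclusion.** The point holds in this limited form. The 80% at N = 34 is valid for Time or Group x Time at a pre-post correlation of 0.5, and it moves between 67% and 95% as the correlation goes from 0.3 to 0.7. For the comparison that the hypothesis needs, it corresponds to a 1.0 SD difference in change. It does not describe the independent t-tests that section 2.6 gives for the non-EEG outcomes, where power at d = 0.5 is about 29%.

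The 29% and 0.99 SD for the independent t-test do not depend on the correlation, and neither does the translation of the interaction f into 1.0 SD. The 80% itself, and the power of Group x Time for a 0.5 SD difference, do. The value 0.5 is inferred because it returns 34; the document does not supply it. A reader might also conclude that the trial must enrol more players. That does not follow, because the fault lies in what the stated power is attached to.

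**What to change.** **Section 2.2.** Name the tested effect and the correlation entered in G*Power (the authors should confirm that it was 0.5), and restate the sensitivity, for example:

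> With 17 players per arm, the Group x Time test has 80% power at two-sided alpha 0.05 for a between-arm difference in pre-post change of about 1.0 SD, assuming a pre-post correlation of 0.5. For a difference of 0.5 SD, power is about 22%, 29%, 45% and 61% at correlations of 0.3, 0.5, 0.7 and 0.8.

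**Section 2.6.** Make Group x Time, which the Discussion already describes, the main between-group test for all outcomes, and keep the t-tests at single time points as supporting description. The choice should be made knowing that at a correlation below 0.5 the Group x Time test has less power for a 0.5 SD difference than the post-intervention t-test (22% against 29% at 0.3), and above 0.5 it has more.

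**Sample size.** Reconcile 34 with the 48 in Table 1. If 48 is the target, restate for 24 per arm: detectable difference about 0.83 SD, with the same assumed correlation of 0.5 for Group x Time, and about 40% power for the independent t-test at d = 0.5.

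The cost is a few sentences and a less favourable statement of what the trial can detect. No extra enrolment and no new measurements are proposed.

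### The recruitment target is given as 34 in the abstract and section 2.2 but as 48 in Table 1, and nothing explains the difference

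*Protocol article*

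**What the plan says.** The abstract gives the number to be randomised: "Thirty-four athletes (17 men, 17 women; aged ≥18 years; ≥1-year competitive experience) will be randomly assigned".

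Section 2.2 (Sample) derives the size with G*Power, "considering a repeated measures ANOVA design with two groups (experimental *vs.* control) factors, and two measurement times (pre *vs.* post"). The inputs are given as "The estimated minimum sample size at alpha 0.05 and statistical power of 80%, for moderate effect size (f = 0.25"), and the result "was approximately 34 subjects (17 per group").

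Table 1, also in section 2.2, has a row on gender balance that reads "Sample of 24 men and 24 women, in equal number for experimental and control groups". That is 24 + 24 = 48.

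On allocation, section 2.2 says that after baseline assessment "all participants will be randomly assigned to either the experimental group or the control group". It gives no method. The pre-post correlation used in the calculation is not stated, and no dropout allowance appears.

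**The concern.** The total and the counts by sex both differ between the two statements, so rounding cannot explain it. The total decides when recruitment is complete, and the power claim is tied to it. A reader of the abstract would call the trial complete at 34 and a reader of Table 1 at 48. Each could say that they followed the published plan. Section 2.1 says that the study will be registered in a public database, and a registration needs a single number.

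The conflict also carries into the sex split. Table 1's balance across arms works with 24 of each sex but not with 17 of each.

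**Working it through.** **The totals side by side**

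| Place | Men | Women | Total |
|---|---|---|---|
| Abstract | 17 | 17 | 34 |
| Section 2.2, text | not given | not given | about 34 (17 per group) |
| Table 1 | 24 | 24 | 48 |

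The difference is 48 − 34 = 14, and 14/34 = 41%. If 48 were 34 inflated for loss, the implied loss would be 1 − 34/48 = 29%.

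**Reproducing the 34**

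Inputs from section 2.2: f = 0.25, alpha = 0.05, power 80%, 2 groups, m = 2 measurement times. The pre-post correlation rho is not stated. I assume 0.5 and show a range.

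For the time-by-group interaction, the noncentrality is lambda = f² × N × m / (1 − rho), with F on 1 and N − 2 degrees of freedom.

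- N = 34: lambda = 0.0625 × 34 × 2 / 0.5 = 8.5; power 80.7%.
- N = 32: lambda = 0.0625 × 32 × 2 / 0.5 = 8.0; power 78.1%.
- N = 48: lambda = 0.0625 × 48 × 2 / 0.5 = 12.0; power 92.4%.

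With equal arms, 34 is therefore the smallest total that reaches 80% at rho = 0.5, and the section 2.2 figure is reproduced. The same inputs do not give 48.

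**Dependence on the unstated correlation**

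| rho | N needed for 80% | Power at 34 | Power at 48 |
|---|---|---|---|
| 0 | 66 | 51.6% | 66.9% |
| 0.3 | 46 | 66.6% | 81.8% |
| 0.5 | 34 | 80.7% | 92.4% |
| 0.7 | 22 | 95.4% | 99.2% |
| 0.8 | 16 | 99.4% | over 99.9% |

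Two variants come close to 48: 80% power at rho = 0.3 and 90% power at rho = 0.5, which both need 46. The article states neither. A test of the between-group main effect does not give 34 at any of these correlations; it needs 66 to 116 participants (98 at rho = 0.5).

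**Sex split**

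- At 48: 24/2 = 12, so 12 men and 12 women per arm.
- At 34: 17/2 = 8.5, so no exact halving. The closest split that keeps 17 per arm is 9 men + 8 women against 8 men + 9 women.

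**The case against.** The best defence is that section 2.2 calls 34 a minimum, so that 48 could be the working target. That fails because the abstract gives 34, with 17 of each sex, as the number to be randomised and not as a floor. Nor is a margin of about 29% stated anywhere, and section 2.4 describes one data collection session.

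Three stronger readings are tempting, and the article does not support them.

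- *The equal sex split is a second, separate error.* The balance is promised only in the Table 1 row that gives 24 + 24, where 12 and 12 is feasible. It becomes impossible only when joined to the abstract's 17 + 17, so it follows from the same conflict. The wording could also mean equal arm sizes, although the row's topic favours balance of the sexes. At 34 the practical gap is 9 against 8.
- *Randomisation is unrestricted, so sex may be badly imbalanced and confound the results.* Section 2.2 is silent on the method, and an article may leave stratification and blocking to the full protocol. Any probability of imbalance would describe an assumed method. Passing and agility are also measured before the intervention, and gender is listed as a covariate (sections 2.2, 2.5.5 and 2.6). This reduces the worry without removing it: the covariates are exploratory, and the independent t-tests at each time point in section 2.6 are unadjusted.
- *The stopping point will be chosen after the data are seen.* Two totals leave room for that, but no interim look is described.

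It also stands in the plan's favour that, at a correlation of 0.5, both totals meet the stated 80% power.

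**Conclusion.** The recruitment target is wrong as written, because 34 and 48 cannot both be the planned total. The difference is 14 participants, or 41% of the smaller figure. This part rests on no assumption.

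The calculation supports 34 for the interaction, but only with a correlation of 0.5, which the article does not state. The 80.7% and 92.4% hold only at that value and should not be quoted without it. If the correlation were 0.3, 34 would give about 67% power and 48 about 82%, so the choice of total could decide whether the 80% goal is met.

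The sex split is a consequence of the same conflict and small in itself. The article does not show a faulty randomisation method.

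**What to change.** 1. State one total in the abstract, the section 2.2 text and Table 1.
2. Beside it, give the assumed pre-post correlation, the power that follows and any dropout margin. If 48 is meant to be 34 plus a margin, say so and state the expected loss.
3. Make the Table 1 split feasible for that total: 12 men and 12 women per arm at 48, or 9 men + 8 women against 8 men + 9 women at 34.
4. If Table 1 means balance of the sexes across arms, say that allocation is stratified by sex so that the promise is met. If it means only equal arm sizes, reword the row.

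Adding sex as a factor in the main models is an optional preference and not part of this correction.

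Reconciling to 34 costs only text edits. Reconciling to 48 commits the study to 14 more participants than the abstract announces. Stratification, if it is not already planned, needs an allocation list by sex.
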